## Methods/design

### Hypothesis

The interaction of various intervention strategies, wherein a supervised workout program, medication review, diet adjustment and health education are included, should achieve further improvements of the neuromuscular and physiological state in the elderly identified as frail, than the standard medical practice.

### Objective

Short-term and mid-term comparison of the efficacy of a multimodal program that incorporates a therapeutic workout program, medication review, diet adjustment and health education, in comparison to the standard medical practice in the improvement of the neuromuscular and physiological condition. Furthermore, it is intended to analyse the maintenance of these effects in a long-term follow-up (12 months) from the onset of the intervention. The workout program consists of a specific part for the development of strength followed by another specific part for endurance training. This sequence has better results than if structured inversely according to previous study [50].

### Design and study patients

The design of the present study is a randomized clinical trial that will be developed in frail elderly people. The present study is a randomized controlled clinical trial conforming to Consolidated Standards of Reporting Trials (CONSORT) guidelines. We refer to hyperfrail to the patients located in the 1/3 of the screening normalized scores, coming from the Clinical Management Unit “Tiro de Pichón”, Health District of Malaga. The inclusion criteria that were established were patients older over 65 years old that, after screening of frailty according to the Short Physical Perfomance Battery (SPPB) series of tests recommended in the Consensus Document by the Ministry of Health, Social Services and Equality on prevention of frailty and falls in the elderly patients, could carry out the program of therapeutic workout [53]. The information and signature of the informed consent are indispensable.

The exclusion criteria established were the presence in the clinical history record of neuromuscular, metabolism, hormonal and/or cardiovascular disorders.

This study will be carried out in accordance with the principles of the Helsinki Declaration to ensure the protection of the rights, safety and welfare of the volunteers that participated in it. Ethical approval of the study will be granted by an Ethical Committee of a public institution [Investigación Provincial de Málaga (Consejería de Salud Servicio Andaluz de Salud, Spain)].

### Outcome measures

Expanded Table 1 with reliability, reference and brief description.

**Table 1 Tab1:** Study variables list

Variable	Type	Value
Socio-demographic		
Gender	Categorical/Dichotomous	Male/Female
Age	Continuous Quantitative	Numeric. Range
Education level	Categorical/Polychotomous	No education/Basic education/Higher education
Clinical		
Risk of falling record	Categorical/Dichotomous	Yes/No
Causes of falling	Categorical/Polychotomous	Intake of psychotropic drugs, presence of urinary incontinence, cognitive impairment, visual problems
Workout	Categorical/Dichotomous	Yes/No
Obesity	Categorical/Dichotomous	Yes/No
FOLLOW-UP		
Body Mass Index (BMI)	Continuous Quantitative	Numeric. Range
General health condition	Continuous Quantitative	SF-12 V2
Fatigue	Continuous Quantitative	POMS (Profile of Mood States)
Frailty	Continuous Quantitative	Inter-Fraitly Questionnaire
Motor control	Continuous Quantitative	Mini-Mental State Examination
Attention – concentration – memory	Continuous Quantitative	WAIS III – Digit Symbol test.
Motor memory	Continuous Quantitative	10 positions – 10 s
Spatial Orientation	Continuous Quantitative	Path reproduction
Grip Strength	Continuous Quantitative	Hand – Grip test
Balance (static, semi-dynamic)	Continuous Quantitative	Time Get-up and Go (extended version)
Gait speed	Continuous Quantitative	Test: 20 m max. Walking speed
Metabolomics	Continuous Quantitative	Systemic inflammation, glucose and lipid metabolism

### Anthropometry

The measurements will be taken following the anthropometric parameter guidelines of The International Society for the Advancement of Kinanthropometry [54] (ISAK)Weight: the subject would be barefooted and in undergarments.Height: distance from the vertex to the sole of the foot. The subject would be standing, in anatomical position and with the occipital region, back, buttocks and heels in contact with the measuring rod. The subject will take a deep breath at the time of measurement while keeping the head in the Frankfort plane.

Body Mass Index (BMI) is obtained dividing the weight in Kilograms (Kg) by the square of height in metres. It estimates the amount of fat and lean mass of the body.

### General health condition using the short form SF-12 questionnaire

General health condition was measured using the SF-12 short form questionnaire, adapted from the extended SF-36 version. Both physical and mental components are evaluated. The higher the score the better the condition. SF-12 reliability has proven a high internal consistency demonstrating an approximate ICC (Intraclass Correlation Coefficient) of 0.9. [55]

### POMS (profile of mood states)

The Spanish version of POMS [56], with 44 items that represented six conceptual dimensions: anger (11 items), fatigue (6 items), vigour (5 items), friendship (6 items), stress (7 items) and depressed state (9 items). As usual, the answer format consisted of a 5 ordered category response, assigned with values 0 (nothing) to 4 (a lot). All the items were put forward in the same trend except for the item 29-relaxed (corresponding to the state of stress) scores, that were inverted after the test.

### Inter-frailty

The auto-administrated survey based in 10 dichotomous questions in order to detect elder frail people will be carried out [57].

### MMSE (mini-mental state examination) – MEC-30 (mini cognitive examination)

The MEC consists of 30 items grouped into 11 sections, the clinician could carry out in 5–15 min based on the following indications; note that those responsible for carrying out this instrument, both in its original version and its Spanish adaptation [58], warn that the professional should stick to these criteria as far as possible, ensuring maximum objectivity in registering the subject’s responses. The eleven sections are: Orientation to time, Orientation to space, Registration, Attention and Calculation, Memory, Nomination, Repetition (Recall), Comprehension, Reading, Writing and Drawing.

### Picture completion test –WAIS III: performance IQ (perception organization index)

This test consists of displaying to the individuals various drawings that lack an important part, which consequently must be named or pointed out within a 20 s time limit [59] The task ends when 5 consecutive faults are committed. The subject is given 1 point per correctly answered item within the time limit. Among the functions involved in this task we distinguish: concentration; perceptual organization; ability to distinguish essential details of the secondary ones; visual recognition of familiar objects; logical reasoning and visual memory. High scores imply: good perception and concentration; good attention to details; ability to carry out and ability to discriminate relevant from irrelevant details. On the other hand, low scores suggest possible anxiety that could affect concentration and concern for unimportant details.

### Motor skill memory test

Motor skill memory and body awareness will be measured directing a test that consists of performing ten static positions. The examiner executes 10 positions holding each one of them for 10 s. Immediately after, the patient imitates the position in the opposite way, analogous to a mirror. The test ends when the 10 positions have been carried out. This test is included in the “Memory in movement” program, used as a cognitive intervention tool [60].

### Spatial orientation dynamic test-revised

The SODT-R (Spatial Orientation Dynamic Test-Revised) [61] task is to direct two moving objects to a given destination. There are two buttons for each of the moving objects in order to control their course. Pressing the buttons changes the object’s course in one direction, reducing or increasing the angular discrepancy between the current course compared to the ideal course that would stand for 0 deviation.

### Hand – grip test

Hand grip strength test will examine the peak of strength and fatigue resistance. The test is performed with the participant in a sitting position and 90 degrees elbow flexion, neutral pronosupination and flexion, extension or inclination of the wrist will not be allowed. The patient will be asked to hand grip, which will be evaluated with a hydraulic dynamometer JAMAR [62].

### Expanded timed up and go

Expanded TUG is a test to assess mobility, balance and risk of falls in the elderly [63]. The test consists of timing how long the seated patient takes to get up, walk ten metres, return and sit back again on the chair.

### Sample size

To achieve a 80% statistical power to detect differences in the statistical hypothesis testing of the null hypothesis H through a bilateral chi-square test for two independent samples, considering that the significance level is 5%, and based on the studies contained in the Consensus Document on Prevention of Frailty and Falls in the Elderly by the Inter-Territorial Council 2014, a priori it is calculated, based on the outcome variable INTERFRAILTY Q included in one of the trials of such literature, by two means and adding a 15% of the losses (it will be necessary to include 100 subjects in the control group- standard medical practice- and 100 subjects in the experimental group – multimodal intervention program) amounting 200 subjects in the study.

### Data collection

The selection of the population that will take part in the study will be chosen through systematic random sampling. The total population consists of the users that belong to the Clinical Management Unit “Tiro de Pichón” medical lists, identified as frail by the nurse’s assessment and that meet the inclusion criteria as described above. The total population will be sorted by alphabetical order. Having determined the sample size, the sampling interval “k” (the skip) will be calculated using the following formula: k = N/n, where “N” is the total population size and “n” is the sample size. We will establish a random number “a” ranging from 1 to “k” that will be the first subject of the study. The remaining sample will be formed by the following elements: a, a + h, a + 2 h, a + 3 h, until the completion of the required sample size (200 subjects) as detailed further. If one of the selected elements wouldn’t be able to take part of the study, the next following element in the initial alphabetically ordered total population listing will be chosen. Figure 1 shows the Flow Diagram is presented from the recruitment to the analysis after the follow-up (12 months).

**Fig. 1 Fig1:**
[figure not shown]
Flow Diagram is presented from the recruitment to the analysis after the follow-up (12 months)

Participants will be handed in a patient handout, in which the study’s course will be detailed, and they will be handed in an informed consent, where it will be stated that their enrolment is absolutely voluntary, hence being possible to leave the study when deemed appropriate. Data protection of the participants will be conducted under the following Law: “Ley Orgánica de Protección de Datos de Carácter Personal 19/55”.

### Control group

The participants in this group will undergo an expository briefing on the importance of performing the exercises and handing in the training schedule in order to strengthen the muscle mass, improve the endurance and reskill balance through working out for 6 months. In addition, a medication review will be taken place and they will be handed in a diet adjustment plan. The data collection along time are the same for both control and experimental groups.

There will be three moments of data collection throughout the intervention: before the intervention, 2 months after the onset and after 6 months. Moreover, there will be a follow-up with two additional measurements: one 3 months and another one 6 months, after the conclusion of the intervention (9 and 12 months from the onset of the intervention, respectively).

The medication review will be focused on the regular, or at least every six months, review of the polypharmacy (intake of more than 5 drugs) insisting on the psychotropic medication due to its greater association to falls and the drugs that can negatively affect people with risk of falling under the STOPP/STAR criteria.

Diet adjustment includes the examination of the variety of nutrients and the protein intake as a protective factor. Anthropometric measurements, weight/height and BMI will be used.

The intervention on the potential hazards at home include conducting the home risk assessment template provided as the Annex 8 of the Consensus document on prevention of frailty and falls in the elderly, and intervening on modifiable elements, obstacles on the floor, mats, cables, lighting type at home, arrangement of the kitchen utensils, bathroom features, type of footwear, clothing and presence of pets.

Team members will reinforce the standard practice by the elements described above in order to improve the condition of frailty.

### Statistical analysis

A descriptive analysis of the socio-demographic variables of the participants will be conducted.

In order to analyse the existent differences in the variable values of interest between the control group and the experimental group, Student’s T-Test will be applied for two independent samples in the case that the normality condition could be accepted, which will be verified by the Saphiro-Wilk test. In case if normality couldn’t be accepted, the appropriate nonparametric test of Mann-Whitey will be conducted.

To analyse the existent differences in the response variables prior to and after the intervention, Student’s T-Test will be carried out for paired samples in the case that the condition of normality could be accepted. In any other case, the appropriate nonparametric test of Wilcoxon will be conducted.

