**Methods:**

A randomized clinical trial of elderly frail patients drawn from the Clinical Management Unit “Tiro de Pichón”, Health District of Malaga, will be included in the study (after meeting the inclusion / exclusion criteria) will be randomized in two groups: a control group that will undergo an intervention consistent of medication review + diet adjustment + health education (regular workout recommendations within a complete advice on healthy lifestyles) and an experimental group whose intervention will consist of a multimodal treatment: therapeutic workout program+ medication review+ diet adjustment + health education. The sociodemographic, clinical and tracing variables will be reflected at the beginning of the study. In addition, the follow-up variables will be gathered at the second and sixth months after the beginning of the treatment and at the third and sixth months after the treatment (follow-up). The follow-up variables that will be measured are: body mass index, general health condition, fatigue, frailty, motor control, attention- concentration- memory, motor memory, spatial orientation, grip strength, balance (static, semi-dynamic), gait speed and metabolomics.

A descriptive analysis of the sociodemographic variables of the participants will be conducted. One-Factor ANOVA will be used for the Within-Subject analysis and as for the Between-Subject analysis, the outcome variables between both the groups in each moment of the data collection will be compared.

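### The planned comparison of the arms leaves out the baseline value that is scheduled for measurement, so a valid test gives away precision by an amount that depends on an unstated correlation.

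*Protocol article*

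**What the plan says.** The Statistical analysis section of the protocol article names the test between control and experimental groups: "T-Test will be applied for two independent samples in the case that the normality condition could be accepted", with normality checked by Shapiro-Wilk and Mann-Whitney used if it fails. The Methods part of the abstract says what this is applied to: "the outcome variables between both the groups in each moment of the data collection will be compared".

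A baseline value is on the schedule. The Experimental group section lists the measurements as "before the intervention, 2 months after the onset and after 6 months", followed by months 9 and 12, and the Control group section gives both arms the same timing.

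Baseline has one use in the Statistical analysis section, a before-and-after test: "To analyse the existent differences in the response variables prior to and after the intervention, Student’s T-Test will be carried out for paired samples", or Wilcoxon if normality fails. The abstract instead names a one-factor ANOVA for the within-subject analysis. Neither is described as comparing the arms. The article describes no between-group change score, ANCOVA or longitudinal model.

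**The concern.** The hypothesis is comparative: the multimodal programme should improve patients more than standard practice does. Yet the analysis that compares the arms does not use baseline, and the analyses that use baseline do not compare the arms.

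If an outcome correlates with its own baseline value, part of its variance at follow-up is predictable before treatment starts. An unadjusted test leaves that part in the error term. Confidence intervals are then wider, and power lower, than the scheduled data allow. This is a method that the article states, so an analysis plan that followed it would carry the loss forward.

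**Working it through.** **Inputs from the article (Sample size section).** 100 patients per arm, 15% allowed for losses, a two-sided 5% level, and power stated as "To achieve a 80% statistical power to detect differences".

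**Inputs the article does not give.** The correlation rho between baseline and follow-up, the standard deviation (SD) and the effect size. Rho is therefore assumed, and a range is shown.

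**Step 1: the plan's own figure.** The total of 100 per arm cannot be reproduced, because no effect size, SD or proportions are stated. Only the allowance for losses can be checked:

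- 100 × (1 − 0.15) = 85 evaluable per arm.
- If the 15% was added by multiplication, 100 / 1.15 ≈ 87.

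**Step 2: implied difference.** If the calculation compared two means, the standardised difference detectable at 80% power is

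d = (1.960 + 0.842) × √(2/n)

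With n = 85 this is 2.802 × 0.1534 = 0.43 SD. With n = 87 it is 0.425 SD. The figure is back-solved and is not a planning value in the article. The same section also names a test of proportions, "through a bilateral chi-square test for two independent samples", and proportions of 0.50 and 0.29 would give 84 per arm, or 99 after the loss allowance. The inputs therefore cannot be recovered from the total.

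**Step 3: effect of adjustment.** ANCOVA multiplies the outcome variance by 1 − rho². The unadjusted t-test then needs n / (1 − rho²) patients per arm to match it. Power of ANCOVA at the Step 2 difference is Φ(2.802 / √(1 − rho²) − 1.960). With n = 85:

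| Assumed rho | 1 − rho² | Equivalent n per arm | Extra per arm for the unadjusted test | ANCOVA power |
|---|---|---|---|---|
| 0.3 | 0.91 | 93.4 | 8 | 83.6% |
| 0.5 | 0.75 | 113.3 | 28 | 89.9% |
| 0.7 | 0.51 | 166.7 | 82 | 97.5% |

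Starting from 87 evaluable per arm, the extra patients are 9, 29 and 84.

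**Step 4: check by simulation.** With 85 per arm and 8,000 simulated trials for each rho, the t-test had 79% to 80% power. ANCOVA had 83%, 89% and 97% at rho 0.3, 0.5 and 0.7, in line with the formula.

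**Step 5: the same loss on another scale.** The patients that ANCOVA could save at equal power are n × rho²: 85 × 0.09 ≈ 8, 85 × 0.25 ≈ 21 and 85 × 0.49 ≈ 42 per arm. These are smaller than the extra-patient figures at the higher correlations, and the two should not be mixed.

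**Step 6: why a covariate and not a change score.** A change score has variance factor 2(1 − rho). Its power on the same basis is 66% at rho 0.3, 80% at 0.5 and 95% at 0.7. It therefore does worse than the planned test below rho 0.5, and worse than ANCOVA at all three values.

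**The case against.** The strongest reply is that the planned test is not wrong. Under randomisation the unadjusted comparison is unbiased and its error rate is correct. That stands, and the point is one of efficiency only.

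The size of the loss is also uncertain. The outcome used for sizing is a survey of ten yes/no questions in patients selected as frail. A restricted range could put its correlation below 0.5, and correlations may fade by month 12. The variance formula is only approximate for the Mann-Whitney branch. All of this stands, and it is why the result is given as a range starting at rho 0.3.

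Three stronger readings are tempting, and the article does not support them:

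- **Chance baseline imbalance as a second harm.** At 100 per arm a chance baseline difference has an SD of √(2/100) = 0.14 SD, about a third of 0.43 SD. Only about rho times this carries into the outcome (0.07 SD at rho 0.5, 0.10 SD at rho 0.7), and the unadjusted standard error already includes it. It is the same precision loss described in another way.
- **Bias from dropout.** A reader might infer that visit-wise tests drop everyone absent at a visit and are biased if the frailest leave. The article does not say how missing visits are handled, which is commonly left to the analysis plan. Bias in the group contrast would also generally need dropout to differ between the arms, in amount or in its relation to outcome.
- **A fixed loss at a primary time point.** The article names no primary visit, and its Sample size section ties the sizing outcome to none. A loss of some 30 to 80 patients per arm cannot be stated as fact, since it holds only if rho is about 0.5 to 0.7.

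**Conclusion.** The point holds as an avoidable loss of efficiency in a stated method, and not as the correction of an invalid test. The direction does not depend on the exact correlation: at any appreciable rho, adjustment gains precision, and near zero it costs almost nothing. The size does depend on it. Matching ANCOVA would take the unadjusted test about 8, 28 or 82 more patients per arm at rho 0.3, 0.5 or 0.7. These figures assume 85 evaluable per arm and the t-test branch. The power figures of about 84%, 90% and 97% further assume that the unadjusted test has exactly 80% power, which implies the back-solved 0.43 SD. The loss will differ by outcome and visit.

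**What to change.** In the Statistical analysis section, replace the visit-wise between-group test with a baseline-adjusted linear model that analyses patients in their assigned arm. Either of two forms will do:

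- ANCOVA at each visit, with the baseline value of the outcome as covariate.
- A repeated-measures mixed model over months 2, 6, 9 and 12, with the baseline value as covariate and group-by-visit terms. This form also uses the earlier follow-up values of patients who miss a later visit.

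The within-arm tests can stay as description but should not carry the comparison of the arms.

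The cost is one degree of freedom for the covariate and slightly more analysis work. No patient, visit or measurement is added. The article reports recruitment as open and no data gathered, so on its account the change can be specified before outcomes are seen.

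### A Shapiro-Wilk pre-test on the trial data chooses between t-test and Mann-Whitney, so the effect measure is not fixed in advance; the Inter-Frailty score would usually lose its comparison of means

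*Protocol article*

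**What the plan says.** The Statistical analysis section of the protocol article compares the two arms with Student's t-test for independent samples where normality can be accepted, "which will be verified by the Saphiro-Wilk test". Otherwise Mann-Whitney is used. Before-after differences go to the paired t-test or to Wilcoxon on the same condition. The section does not state the level of the normality test or what is tested (each arm, the pooled data or residuals).

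The Abstract says the arms are compared at each data collection. The Experimental group section places the post-baseline collections at 2, 6, 9 and 12 months.

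The Sample size section is "based on the outcome variable INTERFRAILTY Q included in one of the trials of such literature", and the calculation is made "by two means and adding a 15% of the losses", giving "100 subjects in the control group" and as many in the experimental group. The same sentence describes the test as being "through a bilateral chi-square test for two independent samples". The Inter-frailty section describes the instrument as "The auto-administrated survey based in 10 dichotomous questions in order to detect elder frail people". Table 1 lists it as continuous quantitative.

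**The concern.** The t-test and Mann-Whitney answer different questions: how far apart the means are, and whether values in one arm tend to exceed those in the other. When a preliminary test on the trial data picks between them, nobody can say beforehand which effect will be tested for a given outcome.

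Two consequences follow.

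- **The outcome used for sizing.** A sum of 10 yes/no items takes only 11 values. At this sample size Shapiro-Wilk can reject such a score through coarseness alone, which would set aside the comparison of means.
- **Comparison over time.** The Objective asks about short-term and mid-term efficacy and about maintenance to 12 months. That needs one effect measure across visits, and a rule applied to each comparison does not guarantee one.

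**Working it through.** **1. Evaluable patients and the stated sample size.** Inputs from the Sample size section: 80% power, two-sided 5%, 15% losses, 100 per arm. Evaluable per arm: 100 × (1 − 0.15) = 85. No effect size, SD or proportions are given, so 100 per arm can only be solved backwards.

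- Two means: detectable d = (1.960 + 0.842) × √(2/85) = 0.43. In the other direction, d = 0.43 needs 85 per arm, and 85/0.85 = 100.
- Chi-square: 50% vs 29% needs 84 per arm, inflated to 99; 40% vs 20% needs 82, inflated to 97.

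Both bases land near 100, so the stated number does not show which was used.

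**2. How often the Inter-Frailty score fails the pre-test.** Assumptions: the score is the 0–10 sum of the 10 items; items are binomial or beta-binomial with mean score 2 to 5 and inter-item correlation 0 to 0.3 (SD about 1.3 to 3.0); Shapiro-Wilk is run at 5%; 85 per arm; 4,000 simulated trials per setting.

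| Mean score | One arm fails | Either arm fails | Pooled residuals fail |
|---|---|---|---|
| 2 | 100% | 100% | 100% |
| 3 | 100% | 100% | 99.9–100% |
| 4 | 96.1–100% | 99.9–100% | 91.8–100% |
| 5 | 78.1–100% | 95.4–100% | 80.3–100% |

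The ranges run over the inter-item correlations. The low single-arm and either-arm values for mean 5 come from correlation 0.1: 1 − (1 − 0.781)² = 0.952, in line with the simulated 95.4%. A repeat simulation put the low end of the either-arm rule at 96%.

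**3. What the pre-test gains or costs in error rates.** In the same settings with no true difference, type I error was 4.6–5.6% for a t-test fixed in advance and 4.3–5.6% for the two-stage rule. At d of about 0.43 (mean 3 to 5, correlation 0 to 0.2), power was 79.4–84.6% for the t-test and 77.7–87.2% for the two-stage rule. The largest gap in any one setting was under 3 points (84.6% vs 87.2%, in favour of the two-stage rule). The pre-test is not needed for validity, and it does little damage to it.

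**4. Switching between the four post-baseline visits.** Assumptions: lognormal outcome (as for a timed test), between-visit correlation 0.6, 85 per arm, either-arm rule.

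| Assumed log-SD | Trials using both tests across the visits |
|---|---|
| 0 (exactly normal) | about 34% |
| 0.15 | about 80% |
| 0.20 | about 64–68% |
| 0.25 | about one third |
| 0.30 | about 11–16% |
| 0.40 | about 1% or less |

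The normal case can be checked by hand. Either-arm failure per visit is 1 − 0.95² = 0.0975. With independent visits, the chance of a mixture is 1 − 0.9025⁴ − 0.0975⁴ = 0.34. If pooled residuals are tested instead, it is about 15–19% (independent visits: 1 − 0.95⁴ = 0.185). At correlation 0.8 the figures at log-SD 0.15 and 0.20 fall to about 68% and 55%. The document gives no SD or between-visit correlation for any timed test.

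For the Inter-Frailty score under the either-arm rule, switching occurred in only 0–3% of trials, except 15% in one setting (mean 5, overdispersion 0.1).

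**The case against.** The strongest reply is that the rule is stated in advance, Mann-Whitney is a legitimate test for an 11-value score, and error rates barely move. All of that is correct. A reader might infer inflated type I error or lost power; step 3 does not support either.

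Other tempting readings also fail or need limits.

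- **That the Inter-Frailty score would be analysed differently from visit to visit.** Under the either-arm rule it nearly always fails the pre-test, so it nearly always gets the same test. Only with pooled residuals and a mean near 5 does switching become common (about 53%), and there the t-test is also used more often (about 19% of comparisons). Switching is mainly a concern for other, near-normal or mildly skewed outcomes.
- **That a large majority of trials would switch tests for timed outcomes.** The figure near 80% sits at the peak of the assumed range; it falls to about 1% with stronger skew.
- **That the trial was certainly sized on means.** The Sample size sentence also names a chi-square test. On that reading neither test in the analysis section matches the sizing. That contradiction needs its own correction.
- **That no mean difference or confidence interval will be reported.** The article names tests and is silent on estimates, which a fuller plan may cover.

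The 0–10 score is itself inferred, since no scoring rule is given. The near-certain rejection applies to scores at a visit; for change scores, simulated as the difference of two independent scores, a single sample failed in only about 19–56% of cases. The before-after wording does not say that the rule runs at each visit.

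What remains is that the data choose the quantity compared, and nothing is gained in exchange.

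**Conclusion.** The point holds as a defect in a stated rule: the between-arm test, and with it the effect measure, depends on a normality result from the trial data. For an Inter-Frailty sum score with about 85 evaluable per arm, Mann-Whitney would be used in about 95–100% of trials under the either-arm rule, or about 80–100% on pooled residuals. The comparison implied by sizing on two means would then rarely be carried out. For other outcomes, the share of trials mixing tests across visits runs from under 1% to about 80%, with the peak near log-SD 0.15.

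These sizes rest on the inferred 0–10 scoring, assumed distributions, a 5% pre-test level and, for switching, an assumed between-visit correlation. The conclusion that the effect measure is unfixed rests on the text alone. The consequence is a weaker comparison of short-term, mid-term and maintained effects and a mismatch with the two-means sizing. It is worth correcting, but it does not threaten the validity of the trial.

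**What to change.** Delete the normality pre-test. Name in advance one between-arm analysis per outcome, the same at every visit: the mean difference with its 95% CI, preferably adjusted for the baseline value, which is already collected. Adjustment is an improvement rather than the cure; adding a covariate while keeping the pre-test would leave the problem in place. Decide in advance whether timed tests are transformed. Keep Mann-Whitney only as a named sensitivity analysis. State how the Inter-Frailty questionnaire is scored, and reconcile the two-means and chi-square wording in the Sample size section so that sizing and analysis agree.

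The cost is a wording change and slightly more analysis work. No extra patients or data are needed, and the change should be made before outcome data are analysed.
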